Hester *et al.*, 2023) and, collectively, professionals feel that they could be more effective. Furthermore, recent evidence suggests that COVID-19 has had a huge impact on the CJS, creating a backlog within an already pressurised process. Extreme delays within the CJS can only exacerbate the issues already present prior to the pandemic.

One innovative approach to diversion from the CJS pathway, “Project CARA”, was developed in 2011, as a conditional caution offered by the police to first time adult offenders of DVA of standard risk according to the DASH domestic abuse checklist and professional judgement. This initiative provided an alternative beyond a ‘simple caution’ or ‘no further action.’ A caution requires the offender to admit culpability in order to be an available disposal option. Hampshire Constabulary in England were ambitious to test an alternative response via an early intervention that would improve outcomes for victim-survivors and their families. Under this model, offenders are required to undertake two mandatory workshops that increase awareness of their abusive behaviour and the safety of partners and children. If, however, they fail to comply with the conditions of this caution, they may be prosecuted for the original offence. In contrast to restorative justice, CARA is an awareness raising intervention for offenders, that utilises a trauma-informed approach and motivational interviewing techniques. In these workshops, offenders are further signposted onto services that support improvements in the wider determinants of their offending behaviour, such as to primary care, drug and alcohol services or onto a community perpetrator programme. Project CARA itself rests on several assumptions about DVA and health inequalities. First, drawing on Marmot
*et al.*, Project CARA recognises the potential lifelong impacts of DVA on health, social and economic outcomes throughout the life-course and aims to tackle the multiplicity of disadvantage and the impact that this can have upon health. Project CARA stresses the importance of early intervention and an understanding that health must not be viewed in isolation, both of which are at the heart of local Health and Wellbeing Board strategies (
Myhill & Bartlett, 2024). An initial experimental trial of CARA was undertaken in Southampton custody suite, showing a reduction in the frequency of re-arrest and prevalence of domestic abuse in the intervention arm, one year following allocation (

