Strang *et al.*, 2017). No further evaluation has been conducted, and both national and qualitative evidence is lacking. Overall the literature is lacking in qualitative evidence around what works for perpetrators, including how to engage them in such interventions, and whether engagement leads to self-awareness and behavioural change. Despite this, CARA has been rolled out nationally and is likely to remain the main-stay intervention for eligible individuals.

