**Figure 1. f1:**
[figure not shown]
Hypothesis 1: Completion of the CARA conditional caution leads to a reduction in incidence and/or severity of DVA at the population level.

**
*Data source*
**: Data held on the police Record Management System (RMS) database, or equivalent, will be extracted, pseudonymised and shared in aggregated form.

**
*Population*
**: The population sample to be included in the analysis are those that are eligible for the CARA intervention.

**
*Intervention*
**: Those who have undertaken the CARA intervention will form the intervention group. CARA is a conditional diversionary caution offered by the police to first time adult offenders of DVA of standard risk or medium risk (in some areas). Offenders are required to undertake two mandatory workshops that increase awareness of their abusive behaviour and the safety of partners and children. In contrast to restorative justice, CARA is an awareness raising intervention for offenders, that utilises a trauma informed approach and motivational interviewing techniques across the pair of workshops. In these workshops offenders are further signposted onto services that support improvements in the wider determinants of their offending behaviour, such as to their GP, drug and alcohol services or onto a community perpetrator programme.

**
*Comparison*
**: Using PSM approaches a comparator group will be formed from those who meet the eligibility criteria for CARA but are based in an area that is currently not delivering the CARA intervention. Covariates for the matching will include demographics, such as age, gender, ethnicity, whether in same sex relationship; offending behaviour/wider determinants, such as offending history and/or risk profile, mental health, employment status, alcohol misuse, accommodation type and; wider contextual factors, such engagement with other perpetrator interventions.

**
*Outcome measures*
**: The primary outcome will be DVA
reoffending within 12 months. The primary outcome will be described as either i) number of DVA arrests ii) number of DVA crimes. The secondary outcome(s) will include for example total number of arrests, crime severity score, total number of offences.

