As our outcome measure (DVA occurrences) are count data, we will also undertake a Poisson model. Calendar quarters will be included as a categorical variable to account for seasonality. The final model will provide a measure of relative risk with 95% confidence intervals to describe the change in incidence in DVA across the CARA sites before and after the introduction of the intervention. We will account for covariates of interest in the final model to examine any changes specific to offender subgroups of interest, including age, sex, ethnicity and socioeconomic status. Confounding events or co-interventions that will affect study outcome will be explored through consultation with the research team, including all stakeholders, and through the qualitative research. Time varying confounders might include, for example, lockdowns from the COVID-19 pandemic.

Where possible we will also aim to undertake a controlled interrupted time series (CITS) (
Bernal *et al.*, 2018). In this case the control data will be derived from sites where CARA was not delivered during the study timeframe. The CITS model can be described as:

Yt-=α+β1Tt+β2Xt+β3XtTt+β4Zt+β5ZtTt+β6ZtXt+β7ZtXtTt

Yt is the aggregated outcome variable measured at each equally-spaced time point (month)

Tt is time

Xt is study phase

XtTt is time after interruption

Zt is treatment or control group

ZtTt is time for treatment and 0 for control,

ZtXt is study phase for treatment and 0 for control,

ZtXtTt is time after interruption for treatment and 0 for control

α, β1, β2 , β3 β4, β5, β6 and β7 are model parameters

**
*Geomapping*
**. We will also undertake geomapping using postcode data from regional and national data (either from the address where the incident took place or the perpetrator’s address). The postcode data will be input using googlemaps to generate a visual-coloured map. The visuals produced through this method are not accurate enough to render an individual’s home address to become identifiable; postcodes are replaced with colour patches, similar to heat maps, covering a large area. The postcodes entered into google through this process are not stored by google and therefore no data will be stored and shared through this method.

**
*Health economics analysis*

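### The matching variables named for the cohort include no calendar time and no shared accrual window is stated, so change over time in recorded offending could partly or wholly mimic a CARA effect

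*Protocol article*

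**What the plan says.** The Comparison paragraph under *Population, intervention, comparison and outcome* in the protocol article sets out the matching: "Covariates for the matching will include demographics, such as age, gender, ethnicity, whether in same sex relationship; offending behaviour/wider determinants". It gives offending history or risk profile, mental health, employment, alcohol misuse and accommodation as examples, and closes with "wider contextual factors, such engagement with other perpetrator interventions". Comparators must meet the CARA eligibility criteria but "are based in an area that is currently not delivering the CARA intervention". The primary outcome is domestic abuse "reoffending within 12 months", described as a number of arrests or a number of crimes.

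On timing, the Introduction says that CARA "was developed in 2011, as a conditional caution offered by the police to first time adult offenders of DVA", was first tried in one custody suite, and that "CARA has been rolled out nationally and is likely to remain the main-stay intervention for eligible individuals". It gives no start date for any force. It also says that "recent evidence suggests that COVID-19 has had a huge impact on the CJS, creating a backlog within an already pressurised process".

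The article deals with calendar time only in the time-series part of *Analysis of quantitative data*. Calendar quarter enters the Poisson model for seasonality, and the text notes: "Time varying confounders might include, for example, lockdowns from the COVID-19 pandemic". The health economics paragraph compares CARA with matched controls and reports cost per reoffence avoided.

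**The concern.** The two groups come into existence under different time constraints. Someone can be a CARA case only if the offence was dealt with after the local force had begun CARA. An eligible person in a non-CARA area can have an index offence at any date for which data are supplied. If nothing aligns those dates, the 12-month follow-up windows of a matched pair may cover different calendar periods.

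This matters because the outcome is recorded arrests or crimes, which depends on police and justice-system activity as well as on behaviour. The article itself says that this activity changed sharply with COVID-19. Matching on age, ethnicity, offending history and similar personal characteristics does not balance calendar time. A time trend, or a lockdown falling mainly in one group's windows, would then be counted as a CARA effect in the primary outcome and carried into the cost per reoffence avoided. The bias could run either way.

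**Working it through.** **Step 1: does anything in the text align the dates?**

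- Matching set: the article names about ten covariates in three classes. None is the date, quarter or year of the index offence.
- Population and Comparison paragraphs: neither gives an accrual window.
- Comparator source: the word *currently* settles which areas qualify. It does not say when the index offences occurred.
- Time series: season and lockdowns are mentioned here only. For the controlled version, control series come from sites without CARA during the study timeframe. This part does not describe the matched cohort.
- Data span: the time series needs data from before CARA and, where possible, from non-CARA sites. Records from periods with no CARA cases may therefore be in the study's data, although the article does not say that the cohort would draw on them.

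Nothing in the article makes the two groups contemporaneous, and nothing forbids it.

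**Step 2: how large could the effect be?** The article gives no reoffending rate, trend, sample size or power for the matched cohort, so there is no figure to reproduce. Everything below is an assumption.

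Suppose CARA has no effect. Let *p* be the 12-month reoffending risk outside an affected calendar period and *p·f* the risk inside it. Let *sC* and *sK* be the shares of CARA cases and comparators in that period. The *p* cancels:

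Spurious risk ratio = (1 − sC + sC·f) / (1 − sK + sK·f)

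| Share in affected period, CARA / comparator | f = 0.8 | f = 1.2 |
|---|---|---|
| 30% / 30% | 0.94/0.94 = 1.00 | 1.06/1.06 = 1.00 |
| 40% / 20% | 0.92/0.96 = 0.96 | 1.08/1.04 = 1.04 |
| 50% / 10% | 0.90/0.98 = 0.92 | 1.10/1.02 = 1.08 |
| 100% / 0% | 0.80/1.00 = 0.80 | 1.20/1.00 = 1.20 |

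Treating the outcome as a proportion, the next table gives the chance of a significant result in the direction of the bias. It assumes two equal groups of 500 to 2,000 and a two-sided test at 0.05. With no bias this chance is 2.5%.

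| Shares | p = 30%, f = 0.8 | p = 20%, f = 0.9 |
|---|---|---|
| 40% / 20% | 6% to 13% | 4% to 5% |
| 50% / 10% | 13% to 39% | 5% to 9% |
| 100% / 0% | 57% to 99% | 12% to 36% |

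**Step 3: the same question as a steady drift.** The null rate ratio is (1 ± annual drift) raised to the mean gap in index dates, in years. For gaps of 1 and 2 years:

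- 5% a year: 0.95 and 0.95² = 0.90 if falling, 1.05 and 1.05² = 1.10 if rising.
- 10% a year: 0.90 and 0.90² = 0.81 if falling, 1.10 and 1.10² = 1.21 if rising.

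**Step 4: what alignment does.** If sC = sK the ratio is 1.00 for every f. This holds only if the calendar effect is the same in CARA and non-CARA areas.

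**The case against.** The strongest reply is that silence is being read as a decision. The covariate list is illustrative, and its last class is open-ended. A condensed article can leave the accrual window and the final propensity model to a fuller document. The authors plainly know about calendar confounding, and in the controlled time series they take controls from the same study timeframe.

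Much of this stands. A reader might infer that the cohort will definitely not be matched on time, that CARA was phased in across forces from 2011, or that a reoffending difference could be expected to be nothing but a calendar effect. The article supports none of these:

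- It does not name index date, but it does not exclude it.
- It gives 2011 as the year CARA was developed, lists no force start dates, and does not say that the cohort data reach back that far.
- Its lockdown remark concerns the time series.
- A large bias needs clearly different index-date distributions, which the article neither states nor implies. With contemporaneous comparators the bias disappears.

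What does not stand is that this is only missing detail. The article chose to set out its matching classes and comparator source, and the difference in when cases can arise is built into that design. Following the named set as written leaves the primary outcome open to a confounder that the plan recognises elsewhere. If index date is not requested before the police data are extracted, a later analysis plan may be unable to restore it.

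**Conclusion.** The point holds in a limited form. The named matching variables include no calendar time, and no common accrual window is stated. Because CARA cases can arise only after a force's start, index dates may differ between the groups, and a change over time in recorded domestic abuse arrests or crimes could then partly or wholly mimic a CARA effect.

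The direction is unknown and the size depends on an imbalance that the article does not give. Under the assumed calendar effects of 20% either way, a mild imbalance moves the null ratio by about 4%, a marked one by about 8%, and complete separation by 20%. The rates, drifts, shares and group sizes used here are all assumptions, so these figures show sensitivity and do not estimate the bias in this study. The matter should be settled before data extraction.

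**What to change.** In the Comparison paragraph:

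- Restrict CARA cases and comparators to a shared calendar period.
- Add calendar quarter and year of the index offence (or of disposal) as an exact or tight-caliper matching variable, and request that field in the police extraction.
- Start the 12-month window from an equivalent anchor in both groups, for example the disposal decision. Choose it so that CARA membership does not depend on remaining offence-free after the clock starts. The article defines the CARA group as people who have undertaken the intervention, which includes two workshops. Starting at the index offence could therefore let early reoffenders drop out of that group. If disposal is the anchor, membership should be settled at disposal too.
- Report the number of CARA cases with no contemporaneous comparator as unmatched.

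A caliper does not give identical follow-up: two 12-month windows offset by 3 months share only 9 months (12 − 3). Exact quarter matching narrows the gap without removing it.

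The costs are that some CARA cases go unmatched and that dates are needed at person level. Both the Data source paragraph and "Ethics and governance" describe the police data as shared in aggregated form, so access to that field has to be confirmed. Alignment also leaves any calendar effect that differs between CARA and non-CARA areas.

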### Analysis of quantitative data

**
*Interrupted time series*
**. Using interrupted time series (ITS), we will also examine whether the introduction of the CARA conditional caution leads to a hypothesised population-based reduction in the incidence of DVA, as hypothesised in Figure 2. A secondary outcome will be to assess if there was a change in the severity of recorded DVA before and after the introduction of CARA.

 As an intervention study design, ITS is a valuable study design compared to traditional observational study designs (such as cohort or case control studies) particularly when there is a need for retrospective evaluations which have already been implemented, either without randomization or to a whole population, both of which are applicable in the CARA intervention (
Bernal *et al.*, 2017). By nature, ITS can be applied to natural experiments when an intervention is introduced at the population level at a clearly defined period of time and involves observing a single population over time.

In an ITS study, a time series of the outcome of interest (incidence of domestic violence and abuse) is used to establish an underlying trend, which is ‘interrupted’ by an intervention (e.g. CARA being offered in a force area) at a known point in time. The pre-intervention underlying trend is compared with the post-intervention period to identify whether the intervention is associated with any changes in outcome.

Initially summary statistics and plots will be undertaken, including a scatter plot of the time series demonstrating before and after comparisons of the incidence of DVA across the force areas. These will include sub-analyses, by age, gender, ethnicity, force area and whether in same sex relationship.

Following this a segmented regression model such as the one below will be constructed to undertake the ITS model:

Yt-=α+β1Tt+β2Xt+β3XtTt

Yt is the aggregated outcome variable measured at each equally-spaced time point (month)

Tt is time

Xt is study phase

XtTt is time after interruption

α, β1, β2 and β3 are model parameters

As our outcome measure (DVA occurrences) are count data, we will also undertake a Poisson model. Calendar quarters will be included as a categorical variable to account for seasonality. The final model will provide a measure of relative risk with 95% confidence intervals to describe the change in incidence in DVA across the CARA sites before and after the introduction of the intervention. We will account for covariates of interest in the final model to examine any changes specific to offender subgroups of interest, including age, sex, ethnicity and socioeconomic status. Confounding events or co-interventions that will affect study outcome will be explored through consultation with the research team, including all stakeholders, and through the qualitative research. Time varying confounders might include, for example, lockdowns from the COVID-19 pandemic.

Where possible we will also aim to undertake a controlled interrupted time series (CITS) (
Bernal *et al.*, 2018). In this case the control data will be derived from sites where CARA was not delivered during the study timeframe. The CITS model can be described as:

Yt-=α+β1Tt+β2Xt+β3XtTt+β4Zt+β5ZtTt+β6ZtXt+β7ZtXtTt

Yt is the aggregated outcome variable measured at each equally-spaced time point (month)

Tt is time

Xt is study phase

XtTt is time after interruption

Zt is treatment or control group

ZtTt is time for treatment and 0 for control,

ZtXt is study phase for treatment and 0 for control,

ZtXtTt is time after interruption for treatment and 0 for control

α, β1, β2 , β3 β4, β5, β6 and β7 are model parameters

**
*Geomapping*
**. We will also undertake geomapping using postcode data from regional and national data (either from the address where the incident took place or the perpetrator’s address). The postcode data will be input using googlemaps to generate a visual-coloured map. The visuals produced through this method are not accurate enough to render an individual’s home address to become identifiable; postcodes are replaced with colour patches, similar to heat maps, covering a large area. The postcodes entered into google through this process are not stored by google and therefore no data will be stored and shared through this method.

**
*Health economics analysis*
**. The aim of the health economic analysis will be to examine the cost-benefits of Project CARA with matched controls. Relevant benefits will include incidents of reoffending and quality adjusted life years (QALYs) obtained from the published literature. Cost considerations will include the cost of delivering Project CARA, including mobilisation and ongoing delivery costs and for both groups we will examine lost economic output, health, legal, social and specialist resources and any personal resource consequences (for example damages, divorce). The perspective of the analysis will include health and social care, criminal and legal and specialist services in the first instance and will explore the inclusion of costs to the victim in a wider cost perspective.

Data sources will include the CARA victim contact form, Crime Survey for England and Wales, and information collected from police taking part in the project. Unit costs will be taken from relevant sources such as the Home Office or Department of Health and Social Care. Results will be presented in a cost-benefit analysis as incremental costs per reoffence avoided and incremental costs per QALY. Probabilistic sensitivity analysis (PSA) will be used to allow for uncertainty around cost and effectiveness estimates.
*
**
**
*

**
*Routine service data*
**. Routine data from the main third sector implementing agencies will be used to examine the fidelity, dose and reach of the CARA intervention. Routine data sources may include, for example, video observations of group work, referral forms and outcome questionnaires. These will be summarised descriptively. All quantitative data sources will be aggregated.

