**Methods:**

Using a concurrent pragmatic mixed methods design model we will undertake a national evaluation of CARA by triangulating quantitative data from up to nine police forces, and routine data from service providers, with qualitative data from workshop participants, victims and professional stakeholders to: (1) understand the long-term impact of CARA implementation on DVA reoffending and engagement with services and (2) explore perceptions and experiences of both delivery and receipt of CARA. We will use qualitative methodologies that draw on interpretivist and phenomenological perspectives, as well as quantitative methodologies using interrupted time series models, Poisson regression models, Geo mapping and a cost benefits analysis.

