## Qualitative study

### Sampling and recruitment strategy

The qualitative study will involve the recruitment of three different population groups:

Phase One: CARA workshop attendees or others, in matters when a simple caution/no further action was the disposal option (referred to collectively as ‘clients’). Where possible, the inclusion criteria for CARA will be used to ensure that participants are broadly comparable.Phase Two: The partner/ex-partner of clients (referred to as ‘victim-survivors’)Phase Three: Professionals and stakeholders comprising CARA facilitators, police staff, and third sector organisations (referred to as 'stakeholders'). It is anticipated that participants will span organisational structures, operational and strategic level roles

In phase 1 and 2, participants will be purposively sampled according to geographical location, socio-economic status, ethnicity, and CARA participation status. Whilst we will aim for gender diversity within our sample, we have not defined this as a primary sampling variable in recognition of the gendered nature of DVA.

Sample size will be guided by the breadth and focus of the research question(s), the demands placed on participants, the depth of data likely to be generated, and the analytic goals and purpose of the overall project. Following recommendations for pragmatic assumptions around sample size (
Braun & Clarke, 2019), it is anticipated that up to 15 clients, 15 victim-survivors and 15 stakeholders will be interviewed.

**
*Phase one*
**. Participants will be recruited from two separate cohorts: (1) a cohort recruited from those involved with or accessing Project CARA workshops, “CARA workshop attendees
*”* within a participating police force area and (2), a cohort of broadly comparable participants without a Project CARA disposal option in a non-CARA participating area. It is anticipated that CARA workshop attendees will be recruited primarily through the [agency] who have responsibility for the design and delivery of Project CARA workshops within the following participating police force areas: Avon & Somerset, Cambridgeshire, Dorset, Hampshire, Leicestershire, Norfolk, Thames Valley, West Midlands, and West Yorkshire. All participants from non-CARA participating areas will be recruited with the support of police staff and third sector organisations who will act as gatekeepers for the study.

**
*Phase two*

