### Population, intervention, comparison and outcome

A previously published study examining the impact of the CARA was undertaken across the West Midlands (
University of Birmingham, 2021). As part of that project a PSM cohort approach was chosen to disentangle the treatment effects from confounding variables which may exist in this study (
Figure 1). However, as this study was only undertaken in one locality it was not sufficiently powered nor contained a diverse enough population to examine whether changes in recidivism or reoffending differed per offender sub-groups in the population such as by age, sex, ethnicity or socio-economic group. Undertaking such an evaluation of these sub-groups would be invaluable in providing further insight into specific groups of offenders who may respond better or worse to the CARA intervention. In this study, we will be able to do this as we are undertaking a nation-wide study to examine the effects of the interventions. Further details on the PSM cohort approach are below:

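### The time-series equations carry one phase term for one aggregated series and no force index, although CARA was adopted at different times; as printed, the pooled level change would be attenuated

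*Protocol article*

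**What the plan says.** All of this comes from the protocol article; no separate analysis plan is shown.

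- **Design rationale** (Analysis of quantitative data, Interrupted time series). ITS is said to apply when an intervention is "introduced at the population level at a clearly defined period of time and involves observing a single population over time". This is a general description of the method, placed just after a statement that features favouring ITS are present for CARA.
- **Model** (same section). The outcome is an aggregated monthly value, the intervention enters through one study-phase term, and a further term gives time after the interruption. All are indexed by time only.
- **Estimate** (same section). The final model is to give a relative risk with a 95% confidence interval to "describe the change in incidence in DVA across the CARA sites before and after the introduction of the intervention".
- **Controlled version** (same section). Where possible, sites that did not deliver CARA serve as controls. The equation keeps the same single phase term and applies it to both groups.
- **Forces.** The Abstract (Methods) plans "quantitative data from up to nine police forces". The qualitative Sampling and recruitment strategy names nine participating areas: "Avon & Somerset, Cambridgeshire, Dorset, Hampshire, Leicestershire, Norfolk, Thames Valley, West Midlands, and West Yorkshire".
- **History of adoption.** The Introduction says CARA "was developed in 2011, as a conditional caution offered by the police to first time adult offenders of DVA" and links this to Hampshire. It adds that "An initial experimental trial of CARA was undertaken in Southampton custody suite". The section Population, intervention, comparison and outcome states that "A previously published study examining the impact of the CARA was undertaken across the West Midlands", citing a 2021 source. The Abstract (Ethics and dissemination) describes national introduction as still under way.

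**The concern.** A single phase term for a summed series needs one date on which the whole population moves from unexposed to exposed. The article's own history implies there was no such date. Whatever month is chosen, forces that started earlier contribute exposed months to the before period, forces that start later contribute unexposed months to the after period, or both.

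Staggered steps also add up to a gradual slope. The time terms in the model will absorb part of that slope as background trend or slope change, which shrinks the level-change estimate.

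The controlled model has a related gap. Control sites never start CARA, so their phase variable needs a borrowed date. With several CARA forces starting at different times, the text does not say whose date that is.

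What is at stake is the population-level result of a national evaluation, which could report a much smaller step than each force experienced. Staggered starts would also help to separate CARA from national shocks such as the COVID-19 lockdowns, which the article names as possible confounders. A single-date fit gives up that advantage.

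**Working it through.** The article gives no start dates, effect size or power calculation for the time series, so there is no stated figure to reproduce. The check asks what the printed model returns when the true effect is known.

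**Assumptions (none from the documents except the count of nine).** Nine equal forces; 84 months; flat underlying trend; an immediate, lasting relative risk of 0.90 in every force from its own start; starts spread evenly around month 42. Expected counts without noise, so every departure from 0.90 is bias.

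**Printed model, log-linear Poisson form, summed series:** log E(Y_t) = α + β1·T_t + β2·X_t + β3·X_t·(time after interruption). The level relative risk is exp(β2).

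**Results with the phase change at the median start:**

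| Spread of starts | Level RR | Share of the 10% reduction lost |
|---|---|---|
| 0 months | 0.900 | 0% |
| 12 months | 0.928 | (0.928 − 0.900)/0.100 = 28% |
| 24 months | 0.952 | 52% |
| 36 months | 0.971 | 71% |
| 48 months | 0.986 | 86% |

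**Where the effect goes, 36-month spread.** Starts fall at months 24, 28, 33, 38, 42, 46, 51, 56 and 60, with the phase change at month 42.

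1. The four late forces contribute 4 + 9 + 14 + 18 = 45 unexposed months to the 9 × 42 = 378 force-months after the date, or 11.9%. By symmetry, 45 of 378 before it are exposed.
2. Misclassification alone, without trend terms: mean after = 0.90 + 0.10 × 0.119 = 0.912; mean before = 1 − 0.10 × 0.119 = 0.988; ratio = 0.912/0.988 = 0.923.
3. With the trend terms the level RR is 0.971. The further loss arises because the fitted underlying trend becomes 0.986 per year when the true trend is flat.
4. With the phase change at the first start instead, the level RR is 0.982, the slope change is 0.978 per year and the fitted RR at the end of the series is 0.88. Here the effect moves into the slope-change term and is not lost.

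**Second set of assumptions.** 96 months, calendar-quarter terms included, phase change at the first, middle or last start: the level RR is 0.923–0.938 for a 12-month spread, 0.946–0.963 for 24, 0.980–0.988 for 48 and 0.993–0.997 for 72.

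**After the fix.** A force-by-month model with each force's own intercept, trend and start date returns 0.90 at every spread tried, under both sets of assumptions.

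**The case against.** The strongest reply is that the article does not commit to the faulty analysis. The rationale sentence describes ITS in general. The text's own illustration of an interruption is a force area beginning to offer CARA, which suits a separate date for each force. The segmented model is offered as an example and the controlled version only where possible. Elsewhere the article uses aggregated to mean not at individual level, so the outcome could be a monthly count per force. One relative risk across sites is also what a properly pooled analysis would report. A missing subscript in a condensed article might be settled in a fuller document.

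Much of this stands, and it limits the point. Four stronger readings are tempting but not supported:

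- **That the plan fixes one calendar date.** It states none.
- **That all nine forces started at different times.** Staggering is documented, but no force's start date is given, and the number contributing data is up to nine.
- **That the analysis would hide the effect.** Part of the lost step can reappear in the slope-change term, as the first-start example shows. A crude before/after ratio without trend is diluted less (0.907–0.943 for a true 0.90 in the 96-month calculation).
- **That Hampshire's trial years will be counted as before, or that the trial was randomised.** The series window is not stated, and the Introduction calls the trial experimental.

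What the reply does not remove: the article chose to print the equations, define their terms and name the estimate, and none of these contains force or a force-specific date. Force area appears only among the sub-analyses of the initial summaries and plots, and it is absent from the covariates listed for the final model. If force-level dates are intended, the printed equations do not express that.

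**Conclusion.** The point holds as a mismatch between the printed model and the adoption history in the same article. Fitted as printed to a pooled series, the model attenuates the level change and moves part of it into the trend terms. For a true relative risk of 0.90, the level estimate is about 0.93 with a 12-month spread of starts and 0.97 with 36 months. These figures rest on nine equal forces, 84 months, an immediate and equal effect, and a phase change at the median start. The spread is an assumption, and the loss is larger or smaller as the true spread is. The point does not show that the investigators will use a single date, only that the text does not provide for several. It should be corrected before the series are analysed.

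**What to change.** Write the model at force-by-month level, for example log E(Y_it) = α_i + β1i·T_t + β2·X_it + β3·X_it·(T_t − s_i) plus the calendar-quarter terms. Here i is the force, s_i is its own start month and X_it is 1 from that month on. Then:

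- State each force's start month, from force records, before the outcome series are examined.
- In the controlled version, give each control series the start date of the CARA force with which it is compared.
- Report a combined relative risk. A panel model or pooled force-specific estimates would both do.
- If Hampshire's series covers the trial period, code that period as a separate phase and not as before.

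The cost is mainly wording, because monthly series and a breakdown by force area are already planned. The start dates must be collected. The combined interval will be somewhat wider, since it will reflect variation between forces.
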